## Abstract

Mental Flexibility oscillates between adaptive variability in behavior and the capacity to restore homeostasis, linked to mental health. It has recently been one of the most investigated abilities in mental and neurological diseases such as Anorexia nervosa and Parkinson’s disease, studied for rigidity or cognitive inflexibility. Patients with anorexia nervosa have rigid cognitive processes about food and weight, which leads to restrictive eating and excessive exercise. People who struggle to adapt their cognitive processes and actions to change their diet and exercise habits may have a harder time recovering from the disorder. On the other hand, research suggests that Parkinson’s disease patients may have cognitive flexibility impairments that impair their ability to perform daily tasks and adapt to new environments. Although of clinical interest, mental flexibility lacks theoretical liberalization and unified assessment. This study introduces "IntellEGO" a protocol for a new, multidimensional psychometric assessment of flexibility. This assessment evaluates a person’s authentic ability to handle daily challenges using cognitive, emotional, and behavioral factors. Since traditional assessments often focus on one domain, we aim to examine flexibility from multiple angles, acknowledging the importance of viewing people as whole beings with mental and physical aspects. The study protocol includes two assessment phases separated by a rehabilitation period. T0, the acute phase upon admission, and T1, the post-rehabilitation phase lasting 15 days for Parkinson’s patients and 4 weeks for eating disorder patients, will be assessed. Neuropsychological performance, self-report questionnaires, psychophysiological measures, and neuroendocrine measures will be collected from Anorexia Nervosa and Parkinson’s Disease patients during each study phase. The objective of this procedure is to provide clinicians with a comprehensive framework for conducting meticulous assessments of mental flexibility. This framework considers emotional, cognitive, and behavioral factors, and is applicable to various patient populations.

## Introduction

Mental Flexibility (MF) is a cross-cutting characteristic that is present in various cognitive-affective processes [1–3]. This concept is commonly delineated in relation to cognitive, physiological, and emotional elements [3–10]. Cognitive flexibility pertains to executive functions, specifically attention shifting and conflict monitoring [9, 11–16]. Psychological Flexibility (PF) or Emotional Flexibility (EF), instead, refers to the individual’s capability to change their behavioral patterns and their willingness to engage with emotions, thoughts, and sensations, including both desired and undesired private experiences [7, 9, 10]. Psychological and emotional flexibility are often considered synonyms in scholarly literature, and for the purpose of this article, the term “emotional” will be employed [6]. All components of cognitive and emotional flexibility exhibit a common characteristic, referred to as *adaptive variability* [3, 17]. Variability refers to the subject’s ability to perceive, respond to, and comprehend events from multiple perspectives [8, 10]. Similarly, adaptability, which refers to the capacity to adapt to different contexts, situations, and challenges to accomplish a specific objective, is frequently connected with resilience and resourcefulness [18, 19]. Therefore, flexible behaviour entails the ability to adjust and modify one’s actions in response to changing situations and methodologies. In addition, previous studies have investigated the cognitive and emotional dimensions in conjunction with various constructs such as emotional intelligence, creativity, beliefs, and mentalizing capacities [11, 12, 14, 20–23]. In fact, the attribute of flexibility arises from the ability to adapt to social interactions, commonly referred to as emotional intelligence. Additionally, it stems from the ability to establish novel connections between ideas and beliefs, known as creativity. Furthermore, having a mindset oriented towards problem-solving, along with the capacity for beliefs and mentalizing, contributes to the development of flexibility. On the other hand, the unfavourable aspects of flexibility encompass rigidity and impulsiveness. Rigidity refers to the inclination to establish and maintain specific cognitive, emotional, or behavioral patterns, which are consistently utilized even in situations where these patterns are no longer advantageous. Rigidity is a psychological construct that has been characterized as the inclination to form and maintain consistent patterns of behavior [24, 25]. Impulsiveness is characterized by a proclivity to engage in rapid actions without due consideration of the potential outcomes, thereby constraining an individual’s capacity to effectively adapt to novel circumstances or contemplate alternative strategies [26–28]. Both problems can be indicative of specific mental health conditions as stated in the Diagnostic and Statistical Manual of Mental Disorders (DSM-5-TR) [24, 25].

In this regard, both the DSM-5-TR and the U.S. National Institute of Mental Health have encouraged psychiatrists to evaluate flexibility in a dimensional manner rather than using categorical assessment. These research domain criteria (RDoC) approach recognizes that flexibility dimensions can transcend traditional diagnostic categories and encourages the integration of multiple levels of data, ranging from genomics to neural circuits to behavior and self-report (for example, using participant-filled questionnaires). This approach aims to understand the fundamental dimensions of functioning that encompasses the entire spectrum of human behavior. The "cognitive systems" domain of the RDoC matrix encompasses constructs such as "cognitive control," "emotion flexibility," and "working memory". These constructs consist of subconstructs, namely goal selection/performance monitoring and flexible updating, which exhibit a robust association with cognitive and emotional flexibility [29]. Cognitive and emotional rigidity or inflexibility are commonly observed characteristics of many mental illnesses [3, 16, 30–35], specifically in clinical conditions that manifest in early life, such as Parkinson Disease (PD) and Anorexia Nervosa (AN). These traits have been extensively documented in the literature with numerous studies specifically examining their presence in PD [30, 31, 33, 36, 37] and AN [38–40].

On one side, recent research has established a correlation between motor stiffness in PD and executive processes (attention shifting and conflict monitoring), which are known to be affected by cognitive procedural rigidity. On the other side, AN is distinguished by its emotional rigidity and difficulties in transitioning between cognitive or affective states. Nevertheless, quantifying this emotional-cognitive rigidity remains unattainable at present. Occasionally, it is overlooked. The lack of evaluation in this context can be attributed to the inconsistent implementation of evaluation methodologies and the difficulties in precisely defining the concept of flexibility, which is currently in the process of being developed. To assess patients with PD and AN in terms of their emotional flexibility, our study describes a comprehensive assessment protocol. This method would enable a more precise restoration of people’s behavioral adaptability and their ability to engage with the external environment (including people, emotions, and situations). The analysis of flexibility can be conducted across various dimensions in order to customize therapy according to the individual needs of the subject.

### Flexibility and Parkinson Disease

PD is a progressive neurodegenerative disorder that exhibits a gradual progression in function. It is characterized by the presence of misfolded α-synuclein protein aggregates in the brain, causing cell death primarily in the substantia nigra and other brain structures [41]. Traditionally, in clinical practice, PD is diagnosed based on the presence of cardinal motor symptoms, namely bradykinesia, resting tremor, and rigidity [42]. In addition to motor symptoms, PD has been documented to manifest rigidity in cognitive and personality domains as well [30, 43]. In the context of PD, individuals affected by this condition demonstrate a notable impairment in their capacity to adapt their current behaviors in order to align with the optimal response required by the surrounding environment. This cognitive ability, commonly referred to as cognitive flexibility, seems to be compromised in PD patients. For instance, Windmann and colleagues [44] hypothesized that impaired switching abilities could potentially be attributed to set-shifting impairments. This hypothesis suggests that the active disengagement from the dominant pattern may be mentally taxing for these individuals. Set-shifting, also referred to as cognitive flexibility, pertains to the ability to effectively adapt to changing environmental demands through the flexible transition between different rules, tasks, actions, and mental sets [26, 45]. Dopamine plays a crucial role in this context. The significance of dopamine in intricate cognitive processes has been widely acknowledged in the literature [28, 46]. The prefrontal cortex of the human brain exhibits a significant presence of dopamine receptors and receives substantial dopaminergic fiber inputs from other regions within the cerebral cortex. The data obtained from PD research indicates that there are early deficits in dopamine pathways caused by the initial degeneration of dopamine neurons in the substantia nigra and ventral tegmental area. As a result, the nigrostriatal dopamine circuitry is impacted by the disease, leading to subsequent damage to the mesocortical and mesolimbic pathways [47]. In this context, it is readily comprehensible to discern the related deficit of PD, which is linked to the role of dopamine and the anatomical structures in which dopamine is located. In fact, abilities traditionally dependent on the integrity of the prefrontal-striatal loops, have been shown to be particularly sensitive to dopamine activity [43]. The cognitive domains commonly affected in individuals with PD as a result of the dopaminergic deficit include working memory, set-shifting, planning, and selective attention. Moreover, researchers suggest dopamine modulates the ability to implement nonroutine schemata and update operations (flexibility processes) [48]. Recent studies also suggest alterations in cognition, are not independent of personality, and emotional disturbance. In particular, researchers provide evidence of a typical emotional and personality pattern of inflexibility, cautiousness, industriousness, and low impulsivity [49], considering that weak set-shifting or cognitive inflexibility results in rigid or perseverative thinking and behavior.

### Flexibility and Anorexia Nervosa

AN exhibits a similar pattern of inflexibility. Extremely low body weight, issues with one’s perception of one’s own weight or body image, and a strong fear of gaining weight are all symptoms of AN [50]. Numerous studies have highlighted the presence of cognitive inflexibility among individuals with AN, as evidenced by both neurocognitive assessments and self-report measures [51–54]. This attribute, in conjunction with challenges related to the processing of emotions, constitutes the principal element of AN [38, 39, 55]. The research conducted by Zhang [56] and Cuesta-Zamora and colleagues [57] provides evidence indicating that specific emotions, such as rage, fear, sadness, and joy, along with longer-lasting and persistent moods, affect dietary responses during the ingestion process. Additionally, it has been noted that rigidity in problem-solving and learning new behaviors, as well as a lack of flexibility in cognition and emotion regulation, affect the maintenance of AN symptoms. These behaviors include weight control and food consumption, fixations with calorie counting, intense exercise, difficulties interacting with others, and rigidity in problem-solving. For instance, it has been demonstrated that emotional dysregulation and low self-esteem play a significant role in the onset and maintenance of emotional disorders [40, 58–61]. Furthermore, recent studies have also found how measures of cognitive flexibility, as measured by neuropsychological tests and those with self-reports, have different impacts on recognizing cognitive inflexibility. Classic neuropsychological tests, such as the Wisconsin Card Sorting Test and Trail making tests, are discriminative in investigating set-shifting problems in advanced disease stages [62]. Self-report tests of cognitive flexibility, on the other hand, would be adapted to identifying behavioral inflexibilities in the early stages of the disease, being related more to activities of daily living [51, 63]. As a result, there is an urgent need for and identification of a multidimensional evaluation aiming at concurrently exploring the emotional-cognitive and biological elements of mental flexibility.

### Objective

The project aims to develop a cognitive affective-behavioral assessment of flexibility in PD and AN patients [62]. The overall goal is to investigate and disentangle flexibility components and their interaction, to create a multidimensional assessment. For this purpose, we will focus on patients characterized by cognitive-affective rigidity problems, such as PD and AN [30, 31, 33, 38–40]. Self-report questionnaires and neuropsychological tests are commonly employed in the evaluation of Cognitive Flexibility (CF), which refers to an individual’s capacity to adapt or transition between different "cognitive sets" or strategies considering environmental changes [64]. Neuropsychological measures classified as "direct" indicate the need for direct observation of the subject’s behavior during various tasks. These measures primarily focus on the cognitive aspect, specifically targeting attentional and mnemonic processes. All these theories are founded on the assumption that transitioning from processing a series of letters to processing a series of numbers necessitates cognitive flexibility and inhibition, as the act of switching to a numerical sequence involves inhibiting the previously processed letter sequence. Self-report questionnaires, on the other hand, are grounded in the assessment of communicative and emotional competencies, interpersonal dynamics, and adaptable emotion regulation strategies. These strategies involve adopting a multifaceted perspective, employing cognitive reframing techniques to manage thoughts and emotions, contextualizing the situation to regulate internal states, and employing cognitive restructuring to mitigate the adverse impact of negative thoughts and emotions. According to a recent meta-analysis, the self-reports and neuropsychological tests assessing "flexibility" did not measure the same underlying construct of flexibility [13, 65]. Furthermore, self-report measures are indirect and retrospective methods of measurement, involving the investigation of emotional behavior by asking individuals to rate a series of statements. Therefore, a dearth of direct quantification of emotional flexibility exists. Consequently, we opted to assess emotional flexibility through direct behavioral analysis utilizing the International Affective Picture System (IAPS). This involved measuring various physiological parameters such as electrocardiogram (ECG), blood volume pulse (BVP), galvanic skin response (GSR), respiration pattern (RSP), facial zygomatic electromyography (EMG-Z) and corrugator (EMG-C), and electrooculography (EOG) [17, 66, 67]. The IAPS picture set has been specifically created to elicit emotional responses. The images within the set are categorized as pleasant, neutral, or unpleasant, and we used it, aiming to explore the range of affective states in a dynamic manner [68–70]. In fact, in recent studies, there has been a considerable amount of research conducted on the temporal changes in affective states, commonly referred to as affect dynamics [71–73]. The objective is to conduct a direct analysis of the transitions from one affective state to another, in order to quantify behavioral and neurophysiological variability as a measure of emotional flexibility [17, 66, 67, 74]. Mental Flexibility has as its main characteristic *adaptive variability*, which in this case comes to be regarded as affective variability.

It would therefore distinguish two major components of Mental Flexibility, cognitive and emotional, which would be examined in both direct (e.g., neuropsychological tests and IAPS) and indirect (e.g., self-reports) terms.

Furthermore, this study aims to assess endocrinological parameters, including interleukin 6, cortisol, serotonin, catecholamines, and endorphins, in individuals diagnosed with eating disorders. These assessments will be conducted at three time points: the beginning of the rehabilitation program (T0), the midpoint of the rehabilitation program, and the conclusion of the rehabilitation program (T1). The selection of these parameters is based on their established correlations with cognitive and behavioral flexibility [3, 75]. For example, previous studies have demonstrated that a temporary reduction in cerebral serotonin levels can impact the cognitive processing of negative feedback in the context of reversal learning [76–78]. Moreover, the utilization of psychostimulants such as methylphenidate, which exert an influence on the activity of dopamine and noradrenaline, has been linked to enhanced attention but possible impediment to cognitive flexibility. In experiments conducted on rhesus monkeys administered therapeutic doses of methylphenidate, researchers have noted a potential negative impact on task-switching abilities [3]. These findings suggest that increased attentional focus may be accompanied by a reduction in cognitive flexibility. Furthermore, it has been observed that the striatal cholinergic systems play a role in influencing behavioral flexibility. Studies conducted on humans using proton magnetic resonance spectroscopy have revealed that a decrease in choline levels within the dorsal striatum is linked to a reduced number of perseverative trials during reversal learning. Previous studies have demonstrated that an excessive expression of IL-6 has the potential to cause cognitive dysfunction by negatively affecting neurotransmission in brain regions that regulate cognitive processes, including the hippocampus and prefrontal cortex. The dysregulation of neurotransmission has the potential to impair cognitive flexibility by causing difficulties in set-shifting and attention [76–80].

Using the proposed multidimensional assessment has the dual objective of investigating the affective, cognitive, and neurobiological components of MF, and its relationships among the different components. In general, people who exhibit greater cognitive rigidity are believed to struggle to change their emotional states: individuals who exhibit higher levels of cognitive rigidity, as assessed through self-report questionnaires and neuropsychological assessments, may demonstrate reduced variability in emotional responses (Fig 1).

**Fig 1 pone.0293921.g001:**
[figure not shown]
Cognitive and affective components of mental flexibility interaction.

Through the process of systematization and analysis, one can gain insight into the cognitive-affective and physiological elements of flexibility. This allows for a comprehensive understanding of the domains that may be most affected and the potential interconnections that exist among these domains. The evaluation of MF presents a novel and intricate task, necessitating the examination of the interplay between its various constituents.

Furthermore, we will collect also emotional and cognitive variables related to mental flexibility (Table 1):

It is predicted that lower emotional regulation scores, emotional intelligence scores, and higher levels of ataxia, anxiety, and depression, as determined by concurrent tests, will be associated with lower levels of flexibility (cognitive and emotional component). Furthermore, in previous research, it has been shown that there is a strong negative correlational association between low levels of mental flexibility and high levels of impulsivity. So, we expect that high levels of impulsivity will correspond to low levels of mental flexibility.Higher levels of flexibility are expected to be associated with better emotion regulation, higher level of emotional intelligence and creativity, as well as lower levels of ataxia, anxiety, and depression and impulsiveness.

**Table 1 pone.0293921.t001:** Concurrent and divergent measures of mental flexibility.

**Higher mental flexibility**	Increase Emotion regulation abilities	Increase Emotional Intelligence		Increase Creativity	Decrease Impulsiveness	Decrease Anxiety and depression
**Lower** **Mental** **flexibility**	Decrease Emotion regulation abilities		Decrease Emotional Intelligence	Decrease Creativity	Increase Impulsiveness	Increase Anxiety and depression

## Method

### Participants

Patients with AN according to DSM-5-TR Diagnostic Criteria [50] aged between 18–45 and patients with PD according to 2015 Movement Disorder Society Clinical Diagnostic Criteria [81] with years range between 45–80 will be recruited. The protocol was approved by the Ethical Committee of the hospital IRCCS Istituto Auxologico Italiano.

For both groups of patients, the following exclusion criteria will be identified:

i) presence of psychiatric pathologies (bipolar disorder, psychotic symptoms, history of psychosis);ii) acute infectious diseases (including infections affecting the respiratory or genitourinary system);iii) chronic inflammatory diseases (including Chron’s disease, and ulcerative colitis);iv) other diseases of the central nervous system (epilepsies, inflammatory or vascular diseases of the central nervous system, genetic diseases affecting the central or peripheral nervous system);v) other medical pathologies in the phase of decompensation that could constitute a confounding factor for the purpose of the study (e.g., tumors, HIV, diabetes mellitus, cardiovascular diseases);vi) tachyarrhythmias, bradyarrhythmias, or other heart rhythm disorders that could compromise the study of heart rate variability.

The last two exclusion criteria apply only to patients with AN:

vii) pregnant women;viii) lactating women.

### Sample size

The sample size was calculated using Gpower 3.1, separately for PD and AN population class. For eating disorders, the study by Sierra and colleagues [82] was used to estimate effect dimension: in the study, IAPS (International Affective Picture System) results were used as a variable dependent on predictive variables describing the emotionality of patients, such as the PANAS (Positive and Negative Affect Schedule). In order to be more conservative and with an effect size of 0.34 and a statistical power of 0.95, we project about 40 subjects, considering eventually drop-out, for the patient and control groups, respectively.

**F tests—**ANOVA: Repeated measures, within-between interaction

**Analysis:** A priori: Compute required sample size

**Input:** Effect size f   = 0.34

   α err prob   = 0.05

   Power (1-β err prob)   = 0.95

   Number of groups  = 2

   Number of measurements = 2

   Corr among rep measures = 0.5

   Nonsphericity correction ε = 1

**Output:** Noncentrality parameter λ = 14.7968000

   Critical F   = 4.1708768

   Numerator df   = 1.0000000

   Denominator df  = 30.0000000

   Total sample size  = 32

   Actual power   = 0.9608705

The study by Ille and colleagues [83] was used to estimate the effect dimension of PD group: The study used IAPS to investigate patients’ emotional reactions. In order to be more conservative and with an effect size of 0.39 and a statistical power of 0.95, we project about 30 subjects, considering eventually drop-out, for the patient and control groups, respectively.

**F tests—**ANOVA: Repeated measures, within-between interaction

**Analysis:** A priori: Compute required sample size

**Input:** Effect size f   = 0.39

   α err prob   = 0.05

   Power (1-β err prob)  = 0.95

   Number of groups  = 2

   Number of measurements = 2

   Corr among rep measures = 0.5

   Nonsphericity correction ε = 1

**Output:** Noncentrality parameter λ = 14.6016000

   Critical F   = 4.3009495

   Numerator df  = 1.0000000

   Denominator df  = 22.0000000

   Total sample size  = 24

   Actual power  = 0.9544574

Control groups will be paired by age and gender relative to patient groups.

Top of Form

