### Statistical analysis

The statistical methodology employed in this study centers around a 2x2 univariate analysis of variance (ANOVA) model. In this model, the between-subjects factor encompasses the distinction between patients and controls, while the within-subjects factor is delineated by the acute phase upon hospitalization (T0) and post-rehabilitation (T1). The primary objective of adopting a univariate approach is to systematically assess the effects of both group membership and time on measures of cognitive flexibility and affective flexibility. Furthermore, we seek to investigate potential interaction effects that may exist between these factors (Fig 4).

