**Fig 4 pone.0293921.g004:**
[figure not shown]
Analysis framework. For each measure of cognitive and affective flexibility an ANOVA 2*2 is implemented with between level of the group (PD/AN vs. Control Group) and within level of time (T0 vs. T1). Then a correlational analysis will be run between cognitive and affective components of flexibility and concurrent measures, considering both T0 and T1 measures.

For assessing Cognitive Flexibility, which involves a diverse array of measurements, we plan to construct a composite score solely relying on self-report data. This composite score will be derived through an Exploratory Data Analysis (EDA) approach employing linear principal component analysis (PCA). By applying PCA, we will extract common underlying dimensions from the various cognitive flexibility self-reports (e.g CFI, CFS, CCFQ, FREE, Dflex) allowing us to aggregate similar items from distinct scales into a weighted average score (Fig 4).

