**Fig 5 pone.0293921.g005:**
[figure not shown]
Markov chain model. From the Core affect model of Russel we can compute 12 complete transitions between affective states, we can insert them in a randomized sequence, calculate transition between blocks and state trait indexes, and once the variability indexes have been relativized, we can fit them into a Markov matrix.

By doing so, we effectively capture the probability of transitioning between and into blocks, empowering to uncover the intricacies of affect dynamics in both music’s auditory realm and images’ visual domain.

From each subject’s data and for each physiological signal, we extracted and analyzed only the main-diagonal indexes, denoted as state trait indexes (AA-BB-CC-DD), which convey the subject’s probability of remaining anchored in a specific affective state (stability).

This meticulous methodology allows us to rigorously assess and understand the dynamics of affective experiences through the lens of Markov chains, offering valuable insights into the temporal evolution of emotional states in our experimental context.

Our anticipated outcomes encompass the following hypotheses:

For participants within the control group, we hypothesize that there will be no statistically significant differences between the scores obtained at T0 and T1, both for measures of cognitive flexibility and affective flexibility. This expectation suggests that individuals in the control group are likely to maintain stable levels of cognitive and affective flexibility over time.Conversely, we expect an interaction effect between group membership (patients) and time (T0 to T1). This interaction effect signifies our hypothesis that cognitive flexibility measures will exhibit improvement over time among patients, leading to concurrent enhancements in affective flexibility. In particular, motor rehabilitation could have a significant impact on executive function, related to mental flexibility, while cognitive-behavioral therapy of individuals with AN could have an impact on both executive function and emotional flexibility.

In essence, our statistical analysis anticipates that patients will demonstrate increased cognitive and affective flexibility throughout the study period.

These hypotheses provide a clear framework for our statistical analysis and offer valuable insights into the expected outcomes of this multifaceted assessment of flexibility.

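### Controls are matched on age and gender, but the stated group-by-time ANOVA contains neither variable, which costs some precision in the patient-control comparison

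*Protocol article*

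**What the plan says.** On selection of controls, the Sample size section says: "Control groups will be paired by age and gender relative to patient groups". It does not say whether each control is tied to one patient or the groups are balanced as a whole. It allows for attrition in the projected numbers (about 40 for AN and about 30 for PD, "considering eventually drop-out, for the patient and control groups, respectively") but gives no withdrawal rate.

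On analysis, the Statistical analysis section says that "the between-subjects factor encompasses the distinction between patients and controls", with T0 and T1 as the within-subjects factor. It aims to assess group membership, time and their interaction. The Fig 4 caption repeats this for every measure: "an ANOVA 2*2 is implemented with between level of the group (PD/AN vs. Control Group) and within level of time (T0 vs. T1". Neither place names age, gender or a pair term. The stated hypothesis concerns the interaction: "we expect an interaction effect between group membership (patients) and time (T0 to T1".

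**The concern.** Matching makes the two groups alike on age and gender, so these variables contribute little to the difference between group means. An ANOVA that omits them still counts the spread they cause within each group as random error. The standard error of the group effect is then larger than the real sampling variation, the test rejects too rarely under the null, and true patient-control differences are harder to see.

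A second, conditional issue concerns withdrawal. If patients leave more often than controls and leaving depends on age, those analysed are no longer balanced on age, and a model without age cannot correct for it.

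At stake is the group comparison, one of the effects that the article sets out to assess. PD eligibility spans ages 45 to 80, so any dependence on age has room to act.

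**Working it through.** **1. The plan's own figures.** Inputs from the Sample size section: f = 0.34 (AN) and 0.39 (PD), alpha 0.05, two groups, two measurements, correlation 0.5. With lambda = f² x N x 2 / (1 - 0.5) and N - 2 denominator degrees of freedom:
- AN, N = 32: lambda = 0.1156 x 32 x 4 = 14.7968, critical F 4.1709, power 0.9609.
- PD, N = 24: lambda = 0.1521 x 24 x 4 = 14.6016, critical F 4.3009, power 0.9545.

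Both reproduce exactly. They are for the interaction, with the groups treated as independent.

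**2. Standard error of the group effect, PD.** Taken from the article: ages 45-80, and about 30, read here as 30 per group. Assumed: uniform age, controls matched exactly on age, 20% withdrawal among patients only and unrelated to age (24 patients, 30 controls), analysis of those remaining, total SD 1 for each person's score, and an age slope b in SD per decade. Gender is left out for simplicity.
- Variance of age = 35² / 12 = 102.08 years² = 1.0208 decades². Share of variance due to age: R² = b² x 1.0208.
- SE without age = sqrt(1/24 + 1/30) = sqrt(0.075) = 0.274.
- SE with age = 0.274 x sqrt(1 - R²).
- Actual SD of the unadjusted difference = sqrt[(1 - R²) x 0.075 + R² x (1/24 - 1/30)]. The second term is small because the remaining patients' ages are a subset of the controls' ages.
- Type I error: the 5% critical t on 52 df, multiplied by SE without age / actual SD, referred back to the t distribution.

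| b | R² | SE without age | SE with age | Actual SD | Type I error |
|---|---|---|---|---|---|
| 0.3 | 0.09 | 0.274 | 0.261 | 0.262 | 4.1% |
| 0.5 | 0.26 | 0.274 | 0.236 | 0.241 | 2.7% |
| 0.7 | 0.50 | 0.274 | 0.194 | 0.204 | 1.0% |

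Separate simulations gave 4.0-4.4%, 2.3-2.7% and 0.8-1.2%. The ratio sqrt(1 - R²) does not depend on group size, so it applies to AN for the same R².

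**3. Withdrawal that depends on age (hypothetical).** Same setting, with log-odds of patient withdrawal rising by 0.7 or 1.2 per decade. The size of the bias in the unadjusted group effect was about 0.04-0.06 SD at slope 0.3, 0.07-0.10 at 0.5 and 0.09-0.15 at 0.7, against a standard error of about 0.27. The unadjusted type I error stayed at or below 5%. With age in the model, bias was at most about 0.006 SD and type I error about 4.6-5.5%. A different parametrisation (R² = 0.2, log-odds 1 per SD of age, roughly 13-33% withdrawal) gave 3.3-5.3% for PD and 3.7-6.3% for AN without adjustment.

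**4. The interaction.** In a 2x2 design this compares T1 minus T0 change between groups. An age effect that is the same at both visits cancels. Simulated type I error was 4.5-5.6% in all settings.

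**5. Would a paired analysis be better?** If matching on age and gender induces no correlation in change, pairing only loses degrees of freedom. At the computed sample sizes, power falls from 0.960 to 0.949 (AN, 16 pairs) and from 0.955 to 0.935 (PD, 12 pairs). It would also discard every pair that loses a member.

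**The case against.** The strongest reply is that the test that matters is the interaction. It drives the sample size and the hypothesis, and step 4 shows that it is sound when age effects are stable. That stands. The error in the group effect is also conservative, so no general excess of false positives follows. That stands too, apart from a slight excess (up to 6.3%) in the most extreme withdrawal setting tried.

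The inputs are assumptions. A slope of 0.7 makes age explain half of all variance. Log-odds of 1.2 per decade means about 2% withdrawal at age 45 and 58% at age 80, during a 15-day stay. Neither is likely, so the lower rows of the table deserve more weight.

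The article is also condensed, and covariates could appear in a fuller plan. However, it names the factors of the model twice and sets group as a target, so a comment on that stated model is fair.

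A reader might go further and infer that the pairing is broken and ignored, that the standard errors are wrong throughout, and that age balance is lost among those analysed. The article does not support this. Its wording on pairing also fits group-level matching, in which there are no pairs to break. It gives no withdrawal rate or pattern. Balance is lost systematically only if withdrawal both differs between groups and depends on age.

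**Conclusion.** The point holds as a minor one about precision. The design controls age and gender, and the stated ANOVA does not use them. For the group effect in PD, the standard error is overstated by about 5% at a slope of 0.3 SD per decade (0.274 / 0.261) and about 16% at 0.5 (0.274 / 0.236), with type I error near 4% and 2.5%. Bias of roughly 0.04-0.15 SD arises only if patient withdrawal depends on age. These sizes rest on assumed slopes, an assumed 20% withdrawal among patients, uniform ages and close matching; the documents give none of the first three. The interaction test is not at fault unless change from T0 to T1 itself depends on age or gender.

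**What to change.** Add age and gender as covariates, with their interactions with time, to the group-by-time model for each measure. Keep every participant with usable data, whether or not a matched counterpart withdraws. State whether matching is individual or by group, and report age and gender balance among those with T1 data. Covariates suit either kind of matching and avoid the losses of a paired test.

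The cost is a sentence or two in the analysis section and a few degrees of freedom. Both variables should already be known for everyone, since they are used to select the controls.
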